## 8.5 Base line assessment

At the initial visit a detailed clinical history will be taken regarding the clinical features and basic demographic details such as age and gender will be recorded. A details medical history regarding past illnesses such as presence of diabetes, hypertension, hyperlipidaemia, asthma and other allergic diseases along with existing liver and kidney failure will be assessed. Those who have existing liver disease or renal disease will be excluded as defined in exclusion criteria. A detailed medical examination will be done and the temperature, heart rate, blood pressure, presence of hepatomegaly or pleural effusions or ascites will be recorded. After examination they will have a FBC done at the hospital and they will be sent home once they are assessed along with the report. They will be advised to come daily to the OPD for assessment and will be educated to seek admission earlier if they develop persistent vomiting, any bleeding manifestations or feel dizzy.

## 8.6 Subsequent Visits

Once the patients are recruited they will be asked to visit the OPD daily for assessment as per National Dengue Management guidelines. During these visits, a detailed medical history regaring vomiting, appetite, how they feel (patient based score), presence of abdominal pain will be recorded. A detailed medical examination will be done and the temperature, heart rate, blood pressure, presence of hepatomegaly or pleural effusions or ascites will be recorded. After examination they will have a FBC done at the hospital and they will be sent home once they are assessed along with the report.

Each patient will be asked to come for 5 visits during acute illness and again 14 days after the onset of illness. The patients will be contacted by phone, 30 days after the onset of illness and a questionnaire will be administered (see follow up described above for details).

**8.7 Discontinuation/withdrawal of participants from the trial**

If a patient takes more than 4 hours to recover from an episode of shock or if a patient goes in to shock for a second time during the illness (after fully recovering from the first episode of shock) we will take him/her out of the trial. Shock is defined as a pulse pressure of ≤20 mmHg or a drop in the systolic blood pressure of 30mmHg or more. Recovery of shock will be defined as an increase in the pulse pressure of >20mmHg or return of the systolic blood pressure to >30mmHg of the patients normal systolic blood pressure. All data obtained prior to that point will be included within the analysis.

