**Secondary end point**

a. Reduction in complications such as liver failure with use of rupatadine. Liver failure will be diagnosed based on the following criteria. All of the 3 following criteria should be present (16).

- Absence of any previously known liver disease
- A prolonged prothrombin time of 4-6 seconds or more
- A INR of >1.5

b. Reduction in development of shock: Shock will be defined as a pulse pressure of ≤20 mmHg or a drop in the systolic blood pressure of 30mmHg or more

c. Reduction in need of colloids: use of dextran will be considered as the patient having significant fluid leakage as per National Guidelines

d. Reduction in need of blood transfusion/s: as per National Guidelines. Use of even 1 blood transfusion will be considered as the patient having significant fluid leakage

e. Reduction in duration of the illness. The first day of the illness will be defined as the day in which the patient developed fever. The day of recovery will be defined when **all** of the following 3 criteria are fulfilled:

- Patient afebrile for 24 hours
- Platelet counts of >50,000 cells/mm^3^ or a rise of 20% from the lowest value
- Return of the haematocrit to the patients baseline

f. Reduction in sleep disturbances: a reduction in sleep disturbances will be assessed by an eight point scoring system, known as the sleep condition indicator (17). This score assessed, difficulty in falling asleep, waking up in the night, quality of sleep, any effect of poor sleep in concentration, relationships, productivity and general wellbeing. The maximum score attainable is 32 and higher scores indicate better sleep quality.

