**Patient follow up**

All patients will be closely monitored during the trial as they will have to visit the study site (OPD) daily for assessment and for blood tests (FBC) as standard management of patients with dengue infection. 4ml of blood will be taken at the OPD for FBCs which are done at the hospital (NIID) as standard management of patients with dengue. All patients will attend daily, and assessed for presence of dengue warning signs and the blood pressure and pulse rate will be recorded. During the visits we will find out the day the patient recovers from illness as defined by the following criteria.

Day of recovery is defined when **all three** criteria below are fulfilled:

-Patient afebrile for 24 hours

-Platelet counts of >50,000 cells/mm^3^ or a rise of 20% from the lowest value

-Return of the haematocrit to the patient’s baselineIf the patient need to attend any OPD visits after the day of recovery, they will be paid Rs. 500 as reimbursement for travel. In each visit the patients will be assessed and monitored in an identical manner.

They will be asked to come 14 days after the onset of illness and the patients general wellbeing will be assessed by patient reported outcome measures including presence of any sleep disturbances (Annexure 3). At the 14 day follow up visit, a blood sample will be taken (4ml) and will be assessed for the presence of dengue IgM and IgG specific antibodies at the Centre for Dengue Research (CDR), University of Sri Jayewardenapura.

The patient will also be contacted 30 days after the onset of illness, by phone to assess the general wellbeing and presence of any sleep disturbances. At the follow up an interviewer administered questionnaire will be used to find out the post viral fatigue and sleep disturbances as previously used in similar studies (17-19). The modified fatigue scale has been previously used to evaluate post viral fatigue following West Nile virus infection (19), which is a viral infection similar to dengue. A fatigue questionnaire has been previously used to evaluate fatigue following dengue infection(18). Before administering these questionnaires to patients in this study (annexure 1), we will validate both questionnaires in this country by translating both to Sinhalese and Tamil.

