## 8.2 Screening and Eligibility Assessment

At the initial visit they will be assessed for the presence of dengue warning signs, their blood pressure and pulse rate recorded and a base line FBC done. If the patient is found to have evidence of fluid leakage or fulfil any of the exclusion criteria in the assessment, he/she will not be recruited.

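### Section 8.7 joins the two recovery-from-shock criteria with *or*, so a patient still in shock can count as recovered and the shock-based withdrawals can be misapplied (minor)

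*Protocol*

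**What the plan says.** Section 8.7 of the protocol has two shock-based withdrawal triggers. The first is prolonged shock: "If a patient takes more than 4 hours to recover from an episode of shock". The second is a repeat episode: "if a patient goes in to shock for a second time during the illness (after fully recovering from the first episode of shock".

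Both depend on two definitions in the same section. Shock: "Shock is defined as a pulse pressure of ≤20 mmHg or a drop in the systolic blood pressure of 30mmHg or more". Recovery: "increase in the pulse pressure of >20mmHg or return of the systolic blood pressure to >30mmHg of the patients normal systolic blood pressure". The shock definition is the same in secondary endpoint (b), under Secondary end point: "Shock will be defined as a pulse pressure of ≤20 mmHg or a drop in the systolic blood pressure of 30mmHg or more".

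On data handling, section 8.7 adds: "All data obtained prior to that point will be included within the analysis". It does not say that data after withdrawal are discarded. Nothing else in the protocol defines recovery from shock.

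**The concern.** Either criterion puts a patient in shock, and either criterion also takes the patient out of it. These two definitions are not opposites. A patient abnormal on both criteria counts as recovered when the first one clears, although the other still meets the definition of shock.

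Two wrong decisions can follow. The 4-hour clock can stop while shock continues, so a withdrawal is missed. Or a brief improvement in one criterion followed by relapse can turn one episode into two, so a patient is withdrawn who should have stayed. These are among the sickest patients in the trial, and two investigators could decide differently from the same chart. A withdrawal may also affect later secondary data: duration of illness, the day-14 visit, and the final call ("The patient will also be contacted 30 days after the onset of illness, by phone").

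There is a smaller matter of phrasing. The pulse pressure criterion speaks of an increase, where a level above 20 mmHg is evidently meant. The systolic criterion evidently means within 30 mmHg of the patient's normal. Neither changes the argument.

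**Working it through.** The protocol states no figure to reproduce here, so the check is one of logic, followed by two invented courses.

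**Inputs (section 8.7).** Let PP be pulse pressure (systolic minus diastolic) and D the fall in systolic pressure below the patient's normal. Both recovery criteria are read as levels.

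- Shock: PP ≤ 20 or D ≥ 30.
- Recovery as written: PP > 20 or D < 30.
- Exact complement of shock: PP > 20 and D < 30.

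**The four possible states**

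| PP | D | In shock? | Recovered, as written (*or*) | Recovered, with *and* |
|---|---|---|---|---|
| 15 | 35 | yes | no | no |
| 25 | 35 | yes | **yes** | no |
| 15 | 10 | yes | **yes** | no |
| 25 | 10 | no | yes | yes |

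The two states with exactly one abnormal criterion are in shock and recovered together. With *and*, recovered is the same as not in shock in every state.

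**Exhaustive check.** Take all integer readings with systolic 50 to 159 and diastolic from 30 to below systolic, and assume a normal systolic of 110.

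- All readings: the sum of (systolic − 30) over the range = 20 + 21 + … + 129 = 8,195.
- D ≥ 30 (systolic ≤ 80): 20 + 21 + … + 50 = 1,085.
- PP ≤ 20: 110 systolic values × 20 = 2,200.
- Both: 31 × 20 = 620.
- Shock: 1,085 + 2,200 − 620 = 2,665.
- Shock and recovered under *or*: 2,665 − 620 = 2,045. Under *and*: 0.

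These counts test the logic only; they say nothing about how many patients are affected. Reading the pulse pressure criterion as a rise of more than 20, or the systolic one as 30 above normal, does not remove the overlap under *or*.

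**Course A, the 4-hour trigger** (assumed normal systolic 110, assumed hourly readings)

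| Hour | BP | PP | D | In shock? | Recovered (*or*) | Recovered (*and*) |
|---|---|---|---|---|---|---|
| 0 | 78/62 | 16 | 32 | yes | no | no |
| 1 | 76/60 | 16 | 34 | yes | no | no |
| 2 | 78/60 | 18 | 32 | yes | no | no |
| 3 | 78/54 | 24 | 32 | yes | **yes** | no |
| 4 | 79/55 | 24 | 31 | yes | yes | no |
| 5 | 80/56 | 24 | 30 | yes | yes | no |
| 6 | 84/60 | 24 | 26 | no | yes | **yes** |

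With *or*, recovery is at 3 h and the patient stays in. With *and*, it is at 6 h, beyond 4 h, and the patient is withdrawn.

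**Course B, the second-shock trigger** (same assumptions)

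| Hour | BP | PP | D | In shock? | Recovered (*or*) | Recovered (*and*) |
|---|---|---|---|---|---|---|
| 0 | 78/62 | 16 | 32 | yes | no | no |
| 1 | 78/54 | 24 | 32 | yes | **yes** | no |
| 2 | 78/60 | 18 | 32 | yes | no | no |
| 3 | 84/60 | 24 | 26 | no | yes | **yes** |

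With *or*, recovery at 1 h and relapse at 2 h make a second shock, and the patient is withdrawn, unless *fully* is taken to mean both criteria. With *and*, it is one 3-hour episode and the patient stays in.

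**The case against.** The strongest reply is that nobody would apply the sentence literally. A patient with PP 15 and D 10 would be recovered at the moment shock began, which makes a 4-hour clock pointless. Each recovery criterion mirrors one shock criterion, in the same order, so the natural reading is that whichever criterion was abnormal must clear. That is a fair reading and it deals with patients abnormal on one criterion. But it is not written, and it leaves open what happens when both are abnormal unless one adds that each must clear.

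The second-shock trigger also requires the patient to have recovered *fully*. On its ordinary meaning that disposes of Course B. The word is undefined, however, and the 4-hour trigger does not use it, so Course A stands.

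The effect on the analysis is limited, and this part of the reply stands. Description of Statistical Methods lists an intention-to-treat analysis that disregards withdrawal. Section 8.4 has every patient treated under the national guidelines, so clinical care does not depend on this wording. Where shock is a serious adverse event (section 10.1), section 8.4 breaks the code and Inclusion in Analysis drops unblinded patients, so some of these patients may leave the analysis however recovery is worded.

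Finally, both courses are constructed, and Course A stays within 2 mmHg of the systolic threshold from 2 h to 5 h. They show that an error is possible, not how often it occurs.

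**Conclusion.** The concern holds as a minor point. As written, recovery overlaps with shock, and the stated rule can give the wrong withdrawal decision in either direction. The clearest case is a patient abnormal on both criteria under the 4-hour trigger; the second-shock error also requires giving no weight to *fully*.

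The consequence is confined to withdrawal decisions and possibly to later secondary data. The any-shock endpoint is unaffected because it depends only on onset. The primary endpoint, fluid leakage, is probably little affected, and no bias between arms is shown. The documents give no shock frequency, so the number of patients cannot be estimated; it is probably small. The logic is certain. The worked courses rest on an assumed normal systolic pressure of 110 mmHg, assumed hourly readings, and both recovery criteria read as levels.

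**What to change.** Replace the recovery sentence in section 8.7 with: *Recovery from shock is a pulse pressure >20 mmHg AND a systolic blood pressure less than 30 mmHg below the patient's normal systolic pressure.* Make both the 4-hour and the second-episode triggers refer to it. This is the exact complement of the protocol's own shock definition, keeps its thresholds, and tidies the loose phrasing in the same edit.

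Keep the patient's normal systolic pressure as the reference. Where it is unknown, use the initial-visit reading, at which patients have "their blood pressure and pulse rate recorded and a base line FBC done" (section 8.2). Whether recovery must also be sustained for a minimum time is a clinical choice for the investigators.

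The cost is a one-sentence amendment and matching case report form wording. No added measurement should be needed: the protocol states no reading interval here, but a 4-hour rule already presupposes repeated blood pressure readings during shock, and the new sentence uses the same ones.

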**8.8 Definition of end of trial**

The trial will end at the last follow up day of the last participant.

# INVESTIGATIONAL MEDICINAL PRODUCT (IMP)

## IMP Description

- The drug will appear as a 10mg tablet
- Patients in the test groups will be given a daily dose of a four 10mg tablets (40mg) orally starting on the day of recruitment for 5 days in addition to the standard treatment as per national guidelines. The control group will receive 4 tablets of the placebo similar to rupatadine for 5 days. Rupatadine will be imported for the study purpose from [name] after approval from SCOCT and NMRA. The placebo will be manufactured by SPMC. The drug and the placebo will be repacked in ensure 5 days of treatment to the study participants.
- As the drug can only be administered orally it will only be given to patients who are able to take drugs orally. At any time point during the study the patient becomes ill and cannot take the drug orally the patient will be taken out of the study. All data collected until the point of withdrawal or until the point of inability to take oral medication will be used in the analysis.
- The placebo will be provided by the State Pharmaceutical Manufacturing Company. The placebo will be identical size and shape to the rupatadine tablet and will not contain ant active ingredients.

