**9.3 Compliance with Trial Treatment**

The nursing officer who offers the drug to the patient will observe the patient taking the first dose of the drug. The patients will be asked to take the subsequent doses at home. At each daily visit, the participants will be asked if they took the drug. If the patient wishes not to take the drug at any time point in the study he/she will be taken out of the study.

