# STATISTICS

## Description of Statistical Methods

The interim analysis will be at half way when half the number of patients are recruited. Statistical significance will be calculated for the interim analysis using the

• χ² test for categorical variables in the two groups

• one-way analysis of variance for continuous variables in the two groups

• Kruskal–Wallis for non-parametric continuous variables in the two groups

• Fisher exact test for categorical variables with small sample size in the two groups ( example when the side effects are small in numbers)

• Intention to Treat (ITT) - ITT analysis will be included as this ignores noncompliance, protocol deviations, withdrawal, and anything that happens after randomization

At the end of the trial, the primary endpoint will be the reduction in the number of individuals who develop DHF. And the secondary efficacy endpoints included duration of reduction in stay at hospitals and side effects. Analysis of covariance (ANCOVA) for the primary endpoint and for secondary endpoints will be used as a statistical method in addition to the above basic statistical methods if applicable. This will be supplemented by a repeated measures analysis.

The effect size will also be computed. Standardized mean difference (SMD), which is used for continuous measures such as leakage, and the number needed to treat, which is used for binary outcomes such as side effects in both groups. The SMD will be computed as the difference between drug and placebo divided by their standard deviation:

SMD = (Drug Improvement - Placebo Improvement) / Standard Deviation

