## Inclusion in Analysis

All randomised participants, all dosed participants, all eligible participants will be included. If and when a patient is unblinded that patient will not be included in the analysis. Any data from a patient who is lost to follow up will be included until that point.

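### Stopping study drug is treated as leaving the study, which conflicts with the promised ITT analysis and can leave DHF status unsettled

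*Protocol*

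**What the plan says.** Three rules end participation.

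- **IMP Description:** a patient who "becomes ill and cannot take the drug orally the patient will be taken out of the study". The same paragraph adds: "All data collected until the point of withdrawal or until the point of inability to take oral medication will be used in the analysis".
- **Section 9.3:** "If the patient wishes not to take the drug at any time point in the study he/she will be taken out of the study". This section has no sentence on which data are kept.
- **Section 8.7:** "If a patient takes more than 4 hours to recover from an episode of shock or if a patient goes in to shock" a second time, "we will take him/her out of the trial". It adds: "All data obtained prior to that point will be included within the analysis".

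The Statistics chapter points the other way. Description of Statistical Methods says: "ITT analysis will be included as this ignores noncompliance, protocol deviations, withdrawal, and anything that happens after randomization". That bullet stands in the list introduced for the interim analysis, but Inclusion in Analysis also takes in all randomised participants. For loss to follow-up, the latter section says: "Any data from a patient who is lost to follow up will be included until that point". The section on missing data provides only for describing its amount.

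Primary Study Endpoints classes patients who are never admitted as having dengue fever only. Admitted patients without leakage by discharge are classed as not having had DHF.

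**The concern.** An ITT analysis needs outcomes that arise after treatment stops. The protocol gives up those outcomes for patients who leave under these rules, and no section says they are collected in another way. A later analysis plan can choose a missing-data method, but it cannot recover outcomes that were never recorded.

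The primary endpoint is exposed because of timing. Treatment starts by about day 3 of illness and runs 5 days, so to about day 7. The background section reports its contrast in pleural effusion height on day 8. A patient removed during dosing may therefore leave before leakage appears. The intensive detection (haematocrit three times a day, daily ultrasound) takes place on the ward, and the protocol itself treats persistent vomiting as a reason to seek admission earlier. Inability to swallow tablets could thus remove a patient just when the endpoint begins to be measured closely. If removal is related to prognosis, or differs by arm, the estimated effect is biased.

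**Working it through.** **1. What each rule costs**

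| Rule | Data kept | Outcomes mainly at risk |
|---|---|---|
| Cannot take drug orally (IMP Description) | To withdrawal or inability | DHF, then later outcomes |
| Does not wish to take drug (9.3) | Not stated | DHF, then later outcomes |
| Shock over 4 h, or second shock (8.7) | Before removal | Colloids, transfusion, liver failure, duration of illness, day-14/30 sleep and fatigue |

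The shock rule differs because the background describes leak as leading to shock, so leakage will normally have been recorded already. The shock endpoint itself is met by the shock that triggers the rule.

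**2. Inputs for an illustration**

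The plan gives no figure for removal, so there is none to reproduce. Planning rates are 42.8% and 23.5% (The Number of Participants); Table 2 shows them as placebo and rupatadine ascites rates respectively, and they are used that way here. The synopsis gives 140 per arm. Alpha is 0.05, taken as two-sided. Power is not stated. At an assumed 90% the pooled formula gives 123 per arm, and 123/0.9 = 137, close to 140.

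**3. Formulas**

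Let w be the assumed share of eventual leakers removed before detection.

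- Scored as no DHF: observed rate = p(1 − w), n = 140.
- Treated as missing, nobody else removed: rate = p(1 − w)/(1 − pw), n = 140(1 − pw).
- Power = Φ[(d − 1.96·s0)/s1], where d is the difference in rates, s0 its pooled standard error and s1 its unpooled standard error.

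**4. Results**

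- *No removal:* d = 0.193, s0 = 0.0563, s1 = 0.0551. Power = Φ(1.50) = 93%.
- *20% in both arms, scored as no DHF:* 0.428 × 0.8 = 0.342; 0.235 × 0.8 = 0.188; d = 0.154, s0 = 0.0528, s1 = 0.0519. Power = Φ(0.98) = 84%.
- *20% in both arms, missing:* n = 128.0 and 133.4; rates 0.374 and 0.197; d = 0.177, s0 = 0.0558, s1 = 0.0549. Power = Φ(1.24) = 89%.
- *20% placebo, 10% rupatadine, scored as no DHF:* 0.342 and 0.2115; d = 0.131, s0 = 0.0535, s1 = 0.0529. Power = Φ(0.49) = 69%.
- *0% placebo, 20% rupatadine, scored as no DHF:* 0.428 − 0.188 = 0.240. The effect is exaggerated by 4.7 points, so bias can run either way.

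**5. Bounds without a scoring rule**

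Suppose 10% of each arm (14 patients, equal to the planned dropout) have unsettled DHF status and the rest follow the planning rates.

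- Least favourable: 0.9 × 0.428 − (0.9 × 0.235 + 0.1) = 0.385 − 0.3115 = 7.4 points (z = 1.29, p = 0.20).
- Most favourable: (0.9 × 0.428 + 0.1) − 0.9 × 0.235 = 0.485 − 0.2115 = 27.4 points (z = 4.81).

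The planned gap is 140 × 0.193 = 27 patients; a 10% loss is 28 patients in total.

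**The case against.** Several stronger readings are tempting, and the documents do not support them.

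- **That ITT cannot be done.** Inclusion in Analysis keeps all randomised patients, and data before removal are retained. The analysis set survives; some outcomes in it are lost, with no rule for handling them.
- **That removed patients count as non-events.** No section says so. It is one possible result of the default for patients never admitted; the missing-data section allows a missing category instead. The scoring matters: 84% becomes 89%.
- **That all the rules cut off the sickest patients before DHF.** A patient who no longer wishes to take tablets need not be worse, and prolonged or repeat shock normally follows leakage.
- **That removal will be frequent or lopsided.** Vomiting in the earlier trial (31.8% rupatadine, 31.3% placebo) is an adverse-event count, not a rate of inability to take tablets, and its near-equality gives no support for unequal removal. A 30% v 10% split would cut power to 39% (63% if missing). It would also mean about 18 placebo leakers, or 12.8% of that arm, which alone exceeds the planned 10% dropout. It should not be used as an estimate.

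It is also fair to say that the end of follow-up is inferred from the removal wording together with the data cut-off; no section states it in so many words. These limits narrow the point. They do not reconcile the removal rules with the ITT statement.

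**Conclusion.** The contradiction is in the text and needs correcting. IMP Description and section 9.3 tie stopping drug to leaving the study, section 8.7 does the same after prolonged or repeat shock, and the Statistics chapter promises an analysis that such removals undermine. The primary endpoint is threatened mainly by the first two rules. The shock rule mainly loses later secondary outcomes.

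Confidence is high for the contradiction and low for the size and direction of bias. Power of 93% falling to 84% or 89% (20% of leakers lost in both arms), or to 69% (20% v 10%, scored as no DHF), rests on assumed removal shares, the planning rates, 140 per arm and a two-sided 5% test. These figures show sensitivity and do not forecast what will happen.

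**What to change.** In IMP Description and sections 9.3 and 8.7, replace removal from the study or trial with wording that study drug is discontinued and the patient stays in the trial. Collect DHF status and the acute secondary outcomes through the acute-illness visits or hospital discharge. Complete the existing day-14 visit and day-30 call unless the patient withdraws consent to follow-up. Delete the sentences limiting analysis to data before removal. Then bring Description of Statistical Methods and Inclusion in Analysis into line: analyse all randomised patients by assigned arm using those outcomes, at the final as well as the interim analysis.

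The rules for when study drug stops are not changed, and no view is taken on them. The cost is amendment wording and a little more data collection, since the daily visits, ward records and both later contacts are already planned.
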